**Fig. 1 Fig1:**
[figure not shown]
Flow chart of study design

### Intervention

#### Investigational products

##### Product I - Tamalakyadi decoction (TMD12)

Traditional TMD12 is a brown-colored liquid, prepared using 5 g of 12 plant ingredients: *Phyllanthus niruri* L.*, Terminalia chebula* Retz., *Premna herbacea* Roxb.*, Piper retrofractum*Vahl*, Piper longum* L.*, Solanum trilobatum* L.*, Tinospora cordifolia* (Thunb.) Miers, *Zingiber officinale* Roscoe, *Piper nigrum* L., *Solanum indicum* L.*, Solanum xanthocarpum* L., *Adhatoda vasica* L.The dried plant materials of the 12 ingredients will be ground separately to pre-prepare a coarse powder pack weighing 60 g containing all 12 ingredients. One 60-g pack of this TMD12 dried powder pack will be used to prepare the decoction needed for 1 day. A 1-week supply (seven packs) of this pre-prepared dried herbs pack will be supplied to the patient. They will be informed to put the supplied herbal pack into a pot, add 1920 ml of water and simmer under low flame until the volume is reduced to 240 ml. The process of preparation under standard conditions will be demonstrated to patients who are selected into the TMD12 arm at the Department of Dravyaguna Vignana of IIM using a video. They will be requested to take a daily dose 120 ml twice a day before meals.

##### Product II - Freeze dried Tamalakyadi decoction (TMD12-FD)

This is a freeze-dried powder prepared from 240 ml of TMD12 decoction (TMD 12- FD), which contains 6 g of TMD12-FD packed in triple laminated sachets under a temperature of 19 ^°^C to minimize the moisture absorbance. Preparation will be done at the Research and Development Complex, Herbal Technology Section, Institute of Industrial Technology, Malabe, Sri Lanka under standard laboratory conditions.

The powder should be dissolved in 240 ml of hot water and 120 ml taken twice a day before meals. This reconstituted powder also contains the above-mentioned 12 ingredients in almost the same quantities. In order to develop a ready-to-use formulation of the TMD 12, with composition similar to the TMD12 after preparation, three different formulations were developed and analyzed [12]. These included freeze-dried formulation, spray-dried formulation, and Ganasara formulation and detailed physicochemical and phytochemical analysis were performed. The results are now published and showed that the freeze-dried formulation is quantitatively and qualitatively closest to TMD 12 [12]. Therefore the freeze-dried formulation was selected for evaluation of clinical efficacy and safety in this clinical trial.

##### Product III - Loratadine 10 mg

Non-sedating antihistamine-loratadine 10 mg was selected as the comparator for this clinical trial. Total quantity of loratadine required for the clinical trial, from one of the leading brands of Loratadine will be purchased from one single batch, directly from the importer for the purpose of the trial. The certificate of analysis of the batch will be obtained to check and ensure the quality of the product used. The purchased products will be stored under 25 °C in an air-conditioned environment at the IIM. Patients allocated loratadine arm are requested to take one tablet daily at evening before meals with 240 ml of water. Details of the investigational drugs are shown in Table 1. To minimize the compliance, patients are advised to submit the patient diary and empty containers of the drugs during weekly visits. Also, the day before the clinic date of every week, the chief investigator will be telephoned and send a text message to a mobile phone to be reminded of the clinic date.

**Table 1 Tab1:** Investigational products

	Drug	Dose	Mode of administration	Route	Method of preparation
1	Tamalakyadi decoction (TMD12)	120 ml	Morning and evening before meals	Oral	60 g (1 packet) of dried powder of plant materials boiled with 1920 ml of water and reduced to 240 ml
2	Freeze dried Tamalakyadi decoction	120 ml	Morning and evening before meals	Oral	6 g (1 sachet) of freeze dried powder dissolve in 240 ml of warm water.
3	Loratadine	10 mg	Evening before meals	Oral	Ingested with 240 ml of water

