## Methods

### Study design

This is a three-arm, open-label non-inferiority randomized controlled clinical trial that will be conducted at the National Ayurveda Teaching Hospital in Colombo, Sri Lanka. TMD12, used in traditional Ayurveda, and its freeze-dried formulation will be the test products. The efficacy and safety of the two Ayurvedic dosage forms will be tested against the antihistamine loratadine. Patients with symptoms of AR will be allocated randomly into the three arms after a 1-week run-in period and the medications given orally for 28 days. This study protocol was developed as required by the Standard Protocol Items: Recommendations for Interventional Trials (SPIRIT) (Additional file 1).

Ethics approval has been obtained from Ethics Review Committee, Institute of Indigenous Medicine (ERCIIM), University of Colombo, Sri Lanka (ERC 18/76) and the Ethics Committee of the Faculty of Medicine, University of Colombo, Sri Lanka (EC-18-090). The trial was registered in the ISRCTN registry (Trial number ISRCTN18149439) (Additional file 2).

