### Storage, packaging, and dispensing of investigational drugs

All three investigational products (herbal materials of decoction, freeze-dried powder, and loratadine) will be packed for 7 days and labeled, which would indicate the batch number, dose, time of administration, mode of administration. These will be stored in the clinic of the Ayurveda Teaching Hospital, Sri Lanka, to be provided to randomized patients according to the predetermined allocation sequence. A supply of drugs for 7 days will be dispensed to the study participants at weekly visits with instructions.

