### Outcome measurements

#### Primary outcome

TNSS of the patients will be used as the primary efficacy endpoint, which has been previously used in allergic rhinitis clinical trials. The mean difference in TNSS will be compared between the three arms at baseline and at the end of 28 days, end of the first month of follow-up and second month of follow-up. The TNSS assesses the symptoms of watery rhinorrhea, nasal obstruction, sneezing, and nasal itching on a four-point scale. The total score range from 0 to 12 where 0 = absent symptoms (no sign/symptom evident), 1 = mild symptoms (signs/symptoms clearly present, but minimal awareness; easily tolerated), 2 = moderate symptoms (definite awareness of signs/symptoms that are bothersome but tolerable), 3 = severe symptoms (signs/symptoms that are hard to tolerate; causes interference with activities of daily living and/or sleep).

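### The stated adherence check asks for the diary and empty containers but not for unused product, so under-use of loratadine may be missed, and the per-protocol set would not remove it

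*Protocol article*

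**What the plan says.** The adherence procedure is in the Protocol article under Product III - Loratadine 10 mg. It refers to drug containers in general, so it appears to cover all three arms: "patients are advised to submit the patient diary and empty containers of the drugs during weekly visits". The purpose given in that sentence is worded the wrong way round: "To minimize the compliance, patients are advised to submit the patient diary".

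Supply is weekly. Under Storage, packaging, and dispensing: "A supply of drugs for 7 days will be dispensed to the study participants at weekly visits with instructions". That section also says that each of the three products is packed for 7 days. For the decoction, "A 1-week supply (seven packs) of this pre-prepared dried herbs pack will be supplied to the patient", one pack per day. Table 1 gives one 6 g sachet per 240 ml for the freeze-dried form, which is one day's amount. For the comparator, "Patients allocated loratadine arm are requested to take one tablet daily at evening before meals with 240 ml of water"; whether the tablets come in blisters, a bottle or single-dose units is not stated.

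The diary appears under Secondary outcomes as a daily rhinitis symptom card, and under Safety assessment as a place to note adverse reactions. Neither section says that doses are entered.

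Method of data analysis plans an intention-to-treat analysis and a per-protocol analysis, the latter limited to patients who complete follow-up. Treatment lasts 28 days, and TNSS is compared "at the end of 28 days, end of the first month of follow-up and second month of follow-up".

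**The concern.** Missed doses are found in containers that are not empty, and those are the containers the instruction leaves out. A patient who skips tablets can comply with it fully and bring back nothing that shows the omission.

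This matters more here than in a superiority trial. If loratadine is taken irregularly, its arm does worse than it should, and the herbal arms can appear non-inferior to a comparator that was not properly delivered. The trial is open-label and recruits partly from the outpatient department of an Ayurveda hospital. The Discussion itself says that some patients choose herbal remedies because they fear the side effects of allopathic drugs. Selective under-use of loratadine is therefore foreseeable, though not shown.

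A smaller matter is that no section shown says leftover product is taken back at day 28, while TNSS is compared again one and two months later.

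**Working it through.** **1. What the returned material can show.** Suppose a patient misses two days in a week.

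| Product | Unit | Returned under the stated rule | What it shows |
|---|---|---|---|
| TMD12 | 7 one-day packs | 5 empties | 7 - 5 = 2 missed days, or 2 lost empties |
| TMD12-FD | 7 sachets, if one is one day's amount | 5 empties | the same ambiguity |
| Loratadine | 7 tablets, container not stated | nothing, if the week's tablets share one container, since it is not empty | one tablet left and seven left look alike |

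Returning the unused units as well settles the ambiguity for the first two rows: 5 empties plus 2 unused packs make 7. It also gives a count for loratadine whatever the container.

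**2. Whether another element fills the gap.** The diary is not described as recording doses. The per-protocol set is defined by completing follow-up, so a patient who attends every visit but skips tablets is in both analysis sets.

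**3. The plan's own figure.** With margin 0.5 SD, two-sided 5% (one-sided 2.5%) and 80% power:

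n = 2(1.960 + 0.842)² / 0.5² = 62.8, so 63 per group; the t-based calculation gives 64, as stated. The illustration below uses n = 64 per arm and one-sided 2.5%.

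**4. Illustration of direction and size.** These are assumptions, not document figures:
- loratadine's full effect E is 0.57 to 0.67 SD, the range cited under Sample size;
- the effect falls in proportion to the fraction m of missed doses;
- only one arm under-uses at a time.

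SE = √(2/64) = 0.1768 SD.

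*Loratadine missed, with the test product truly worse by exactly the margin.* The observed deficit shrinks by E × m, so P(false non-inferiority) = Φ(E·m/SE - 1.960).

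| m | E·m (SD) | False non-inferiority |
|---|---|---|
| 0 | 0 | 2.5% |
| 10% | 0.057-0.067 | 5.1-5.7% |
| 20% | 0.114-0.134 | 9.4-11.5% |
| 30% | 0.171-0.201 | 16.0-20.5% |
| 50% | 0.285-0.335 | 36.4-47.4% |

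*Test product missed instead, with the two products truly equal (so E is also the test product's effect).* Power = Φ((0.5 - E·m)/SE - 1.960). At m = 0 this is Φ(0.868) = 81%. At m = 20% it is 59% for E = 0.57 and 54% for E = 0.67. Under-use of a herbal arm thus works against non-inferiority.

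**5. Leftovers.** If a full week's supply is handed out at each of the four weeks whatever remains, leftover daily units = 28 × (1 - adherence): 2.8 at 90%, 5.6 at 80% and 8.4 at 70%. These adherence rates are assumed.

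**The case against.** The strongest objection is that this is a condensed article. Drug accountability often sits in the full protocol, and the Study procedures table and the flow chart cannot be seen here. Silence about tablet counts would not be a finding. That is right as far as it goes, but the article does state an adherence rule, and the rule names the less informative material. The point rests on that wording.

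A reader might infer more than the text supports:

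- **That empties are the only check, that unused product is never counted or collected, and that under-use goes unseen.** None of this follows. The diary is named in the same sentence, no section says that leftovers are not collected, and with one-day packs a shortfall in empties does hint at missed days. The method is weak, not blind.
- **That the bias must favour non-inferiority.** The Background says that daily decoction preparation is hard to fit into busy lives, and the decoction has to be boiled down from 1920 ml to 240 ml each day, against one tablet. Under-use there acts in the opposite direction, so the net effect is unknown.
- **That at 70% adherence loratadine's effect would fall below the margin** (0.57 × 0.7 = 0.40 and 0.67 × 0.7 = 0.47, against 0.5 SD). This takes the cited range as loratadine's full effect and scales it linearly. The article does not say what those effect sizes contrast, and the comparison mostly reflects how large the margin is, which counting tablets cannot change.
- **That leftovers will distort the follow-up scores.** Nothing shows that a few retained units would be taken, or would alter TNSS one or two months later.

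Two further objections stand. Counting unused whole-day units cannot reveal a missed half-day dose or a discarded one. And a count changes no stated analysis unless the per-protocol definition uses it.

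**Conclusion.** The concern holds in limited form. As written, the check cannot separate missed doses from lost empties for the herbal products and is least informative for the comparator, where under-use would favour the trial's conclusion. Neither stated analysis set would exclude under-users.

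The actual size cannot be given, because the document states no adherence rate for any arm. The figures above show only that moderate under-use confined to loratadine could matter: under the listed assumptions, 20% missed doses raise a nominal 2.5% error to roughly 9-12%. Retained product during follow-up is a secondary reason for the same change. The reversed wording about compliance is an evident slip with no effect on the trial's validity.

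The change is worth making because weekly visits already take place, and the article reports recruitment as still in progress.

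**What to change.** 1. In the adherence instruction, ask patients to bring all containers, used and unused, with any remaining product.
2. At each weekly visit and at day 28, count unused tablets, packs and sachets against the seven dispensed, and enter the count in the case record form so that it can be tabulated by arm.
3. Take back leftovers by day 28, so that none remain with patients for the one- and two-month TNSS assessments.
4. In Method of data analysis, report adherence by arm and add a criterion based on the count to the per-protocol definition, fixed by the sponsor before the results are examined.
5. Replace the word "minimize" in the compliance sentence with the one intended.

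The cost is one line of patient instructions, one form field and a few minutes per visit, with no extra visits. Patients treated before the change will lack counts, and this should be stated when adherence is reported.

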### Storage, packaging, and dispensing of investigational drugs

All three investigational products (herbal materials of decoction, freeze-dried powder, and loratadine) will be packed for 7 days and labeled, which would indicate the batch number, dose, time of administration, mode of administration. These will be stored in the clinic of the Ayurveda Teaching Hospital, Sri Lanka, to be provided to randomized patients according to the predetermined allocation sequence. A supply of drugs for 7 days will be dispensed to the study participants at weekly visits with instructions.

### Outcome measurements

#### Primary outcome

TNSS of the patients will be used as the primary efficacy endpoint, which has been previously used in allergic rhinitis clinical trials. The mean difference in TNSS will be compared between the three arms at baseline and at the end of 28 days, end of the first month of follow-up and second month of follow-up. The TNSS assesses the symptoms of watery rhinorrhea, nasal obstruction, sneezing, and nasal itching on a four-point scale. The total score range from 0 to 12 where 0 = absent symptoms (no sign/symptom evident), 1 = mild symptoms (signs/symptoms clearly present, but minimal awareness; easily tolerated), 2 = moderate symptoms (definite awareness of signs/symptoms that are bothersome but tolerable), 3 = severe symptoms (signs/symptoms that are hard to tolerate; causes interference with activities of daily living and/or sleep).

#### Secondary outcomes

The following four symptom scores will be used as secondary end points.
Mean score of daytime nasal symptomsMean score of night time nasal symptomsMean score of non-nasal symptomsPatient’s self-rated symptom scores (daily rhinitis diary card) and allergic rhinitis grading symptoms will be used as secondary measures of the efficacy in the clinical trial. Such symptom scores will be collected on a weekly basis during the assessment period. The measurement of symptoms on a four-point rating scale with the following definitions will be used.
= absent symptoms (no signs/symptoms evident)= mild symptoms (signs/symptoms clearly present, but minimal awareness; easily tolerated)= moderate symptoms (definite awareness of signs/symptoms that are bothersome but tolerable)= severe symptoms (signs/symptoms that are hard to tolerate; causes interference with activities of daily living and/or sleep).Mean score of health-related quality of life score – Health-related quality of life is measured using allergic rhinitis symptoms at the baseline and end of the intervention (after 4 weeks, 1 month of follow-up, and 2 months of follow-up).

Changes in the serum IgE level and eosinophil count will be studied by comparing before and after treatment values. Procedures related to the study are shown in Table 2.

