## Method of data analysis

For primary and secondary outcome measures, the mean values at baseline and at the end of the study and the mean differences will be compared between the three arms using ANOVA (analysis of variance) or the non-parametric Kruskal–Wallis test, depending on the normality of the data. Within each treatment arm, the difference in primary and secondary outcome measures before and after the intervention period will be compared using paired-sample *t* test or non-parametric Wilcoxon signed-rank test, depending on the normality of the data. 95% confidence intervals will be calculated for all outcome measures that are normally distributed. Categorical variables will be compared between groups using the Chi-square test. Possible confounders will be adjusted using ANCOVA. Following adjustment for confounding using ANCOVA, adjusted mean values with confidence intervals will be calculated and reported. Statistical analysis will be performed using the SPSS Statistical Package program (ver. 18.0), and the level of significance will be established at α = 0.05. Missing data at outcome assessment will be replaced with the available latest values of the outcome measure. Intention-to-treat analysis will be performed for all efficacy outcomes and safety outcomes. In addition, per-protocol analysis will be performed for the efficacy outcomes by including only the patients completing the follow-up.

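### If serum IgE and eosinophil count are skewed, the stated ANOVA/Kruskal-Wallis rule loses power and gives no interval for either TMD12 arm against loratadine; a log-scale, baseline-adjusted model would give both

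*Protocol article*

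**What the plan says.** All references are to the protocol article.

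- **Secondary outcomes.** The section opens with "The following four symptom scores will be used as secondary end points". After that list a separate sentence adds the two markers: "Changes in the serum IgE level and eosinophil count will be studied by comparing before and after treatment values". It states no scale, transformation or between-arm contrast.
- **Method of data analysis, between arms.** One rule is set for the main endpoint and the secondary ones alike: "the mean values at baseline and at the end of the study and the mean differences will be compared between the three arms using ANOVA". Kruskal-Wallis is the alternative when normality fails.
- **Same section, within arms.** A paired t test, or its signed-rank counterpart, is planned: "the difference in primary and secondary outcome measures before and after the intervention period will be compared using paired-sample".
- **Same section, intervals.** The general promise reads: "95% confidence intervals will be calculated for all outcome measures that are normally distributed".
- **Same section, adjustment.** "Possible confounders will be adjusted using ANCOVA", after which "adjusted mean values with confidence intervals will be calculated and reported". The covariates are not named, and no normality condition is attached to these intervals.
- **Study design.** "This is a three-arm, open-label non-inferiority randomized controlled clinical trial". The same section says that both herbal dosage forms are tested against loratadine.

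**The concern.** TNSS, the daytime, night-time and non-nasal symptom scores and the quality-of-life score are all ratings made with the treatment known. The two blood markers are the only efficacy-type measures that are not. As supportive evidence they are useful only if the analysis gives an estimate of each TMD12 arm against loratadine, with an interval.

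Markers of this kind take positive values and are often right-skewed. If these are, the stated rule sends them to a three-arm Kruskal-Wallis test. Its P value says whether the arms differ somewhere, but gives no effect size against loratadine, and the general interval rule no longer applies. If they are kept under ANOVA instead, mean differences on the raw scale are driven by the few patients with the highest starting values.

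**Working it through.** **1. Sample size behind the check.** The article gives 64 per arm for TNSS, from a standardized margin of 0.5, 80% power and 5% significance. n = 2(1.960 + 0.842)²/0.5² = 62.8, so 63 by the normal approximation. The t-based solution is 63.8, so 64. The stated figure is reproduced, but it was set for TNSS. No size, SD or expected effect is given for either marker.

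**2. Model for the check (all assumed).** Lognormal markers; a proportional treatment effect, equal in both TMD12 arms; three arms of 64; two-sided 5%. Three analyses were compared: ANOVA on raw change, Kruskal-Wallis on raw change, and ANCOVA of log post-treatment value on arm and log baseline:

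log(post) = a + b·log(baseline) + c₁·[TMD12] + c₂·[TMD12-FD] + error; ratio to loratadine = exp(c).

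**3. First set of assumptions.** Between-patient SD of the log value 0.6 to 1.2, within-patient SD 0.2 to 0.3, true ratio 0.85 or 0.80. The implied before-after correlation on the log scale runs from 0.36/(0.36 + 0.09) = 0.80 to 1.44/(1.44 + 0.04) = 0.97.

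- ANOVA on change: power 0.19 to 0.94
- Kruskal-Wallis on change: 0.42 to 0.98
- Log ANCOVA: 0.59 to 1.00
- Gain of log ANCOVA over the rank test: about 8 to 19 points, except where the rank test already reaches 97-98%
- With no effect, rejection was near 0.05 for every method

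**4. Second set, by SD of the log value, correlation r and true ratio** (2000 simulated trials per row):

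| SD, r, ratio | ANOVA, change | Kruskal-Wallis, change | ANCOVA, raw baseline | ANOVA, log change | ANCOVA, log |
|---|---|---|---|---|---|
| 1.2, 0.95, 0.80 | 0.402 | 0.797 | 0.518 | 0.946 | 0.953 |
| 1.2, 0.95, 0.85 | 0.246 | 0.524 | 0.298 | 0.702 | 0.708 |
| 1.2, 0.90, 0.80 | 0.236 | 0.511 | 0.312 | 0.667 | 0.694 |
| 1.0, 0.90, 0.80 | 0.395 | 0.654 | 0.500 | 0.828 | 0.843 |
| 1.5, 0.95, 0.80 | 0.172 | 0.586 | 0.240 | 0.802 | 0.801 |
| 0.6, 0.5, 0.80 | 0.422 | 0.455 | 0.596 | 0.564 | 0.682 |
| 0.6, 0.7, 0.80 | 0.614 | 0.688 | 0.763 | 0.805 | 0.860 |
| 0.7, 0.6, 0.75 | 0.532 | 0.626 | 0.736 | 0.769 | 0.868 |
| 0.8, 0.6, 0.75 | 0.382 | 0.499 | 0.548 | 0.641 | 0.742 |
| 1.2, 0.95, 1.00 (no effect) | 0.038 | 0.056 | 0.044 | 0.054 | 0.053 |

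The gain over the rank test runs from 0.953 − 0.797 = 16 points to 0.742 − 0.499 = 24 points. It is larger than in the first set mainly where the correlation is lower, because baseline adjustment then adds to the gain from the log scale. In the first five rows nearly all the gain comes from the log scale; in the next four, part comes from the baseline term.

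**5. Width of the interval the plan does not provide.** For one TMD12 arm against loratadine, the 95% limits are the estimated ratio divided and multiplied by exp(1.96·SD·√(1 − r²)·√(2/64)).

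- SD 1.2, r 0.95: exp(1.96 × 1.2 × 0.312 × 0.177) = 1.14
- SD 0.8, r 0.6: exp(1.96 × 0.8 × 0.8 × 0.177) = 1.25
- SD 1.2, log end values only, with no baseline term: exp(1.96 × 1.2 × 0.177) = 1.52

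**The case against.** **The scale is a matter for the analysis plan.** This stands in part. That plan is not shown and could add a transformation, and nothing in the article forbids one. But the article is not silent: it states that non-normal data go to a rank test and that general intervals are for normally distributed outcomes. A log-scale estimate would change that stated rule.

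**The plan does not say absolute change.** Correct. A reader might infer that the markers must be analysed as absolute before-after differences. The text says only before and after values and mean differences, and it compares end-of-study values as well. It is also not certain that the data-analysis section covers the markers, since they stand outside the four named secondary endpoints.

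**ANCOVA is already provided, with intervals.** Correct, so it would be too strong to say that the plan offers no estimate of any kind. What remains is narrower: the intervals are for adjusted arm means, not differences from loratadine, and the baseline marker value is not named. If it were entered on the raw scale, power was 0.24 to 0.52 in the first five rows of the table. In the next four rows raw ANCOVA did better than the rank test, but stayed below log ANCOVA.

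**The markers carry little weight.** This largely stands. Nothing in the article says that either should move within 28 days or track TNSS, and the non-inferiority conclusion rests on TNSS. A reader might also call them the only outcomes that opinion cannot shift, but the laboratory tests under Safety assessment are objective too. The claim is limited to efficacy-type measures.

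**The simulation favours the log model.** The distributions are assumed and a proportional effect suits that model. It was also ahead in two checks with an additive effect, but those do not settle the size of the gain. The missing interval under the rank branch does not depend on any simulation.

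**Conclusion.** The point holds as a low-cost improvement of minor severity. If the data-analysis section governs the two markers and they are right-skewed, the stated rule gives a three-arm rank P value and no interval for either TMD12 arm against loratadine. At 64 per arm the rank test then has roughly 8 to 19 points less power than log ANCOVA, except where it is already near 100%; the second set of assumptions gives about 16 to 24 points. These figures rest wholly on assumed SDs, correlations and effects, because the article gives none for the markers.

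Two stronger readings are not supported. The false-positive rate is not affected: under no effect every method rejected at about 5%. And the trial's main conclusion is not in doubt on this account, since the markers are supportive and the trial was not sized for them.

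**What to change.** Add to the data-analysis section that serum IgE and eosinophil count are log-transformed and analysed by a linear model of the log post-treatment value on arm and log baseline value. Report TMD12 to loratadine and TMD12-FD to loratadine, each as a ratio of geometric means with 95% CI. State that this replaces the before-after comparison as the main result for these two markers, and that they are supportive.

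Fix the rule for zero eosinophil counts before the data are seen, including the value of any added constant, because that choice can shift the ratio when counts are low.

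The cost is wording only: no new samples, visits or tests. Trial status says that recruitment was still in progress, so the change can precede the analysis. The drawbacks are that results are read as ratios rather than in laboratory units, and that the constant must be settled beforehand.
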